## Abstract

**Background:**

Lifestyle interventions have potential to support people with Parkinson’s disease (PD) in self-managing their disease and improving quality of life. Growing evidence suggests positive effects of singular lifestyle interventions, such as physical activity, stress or nutrition. However, several challenges remain. First, despite potential additive and perhaps even synergistic effects, research on combining lifestyle interventions is limited. Second, lifestyle interventions are not routinely addressed as part of standard medical care. Finally, there are significant challenges related to changing behavior and adherence to lifestyle interventions. This study aims to evaluate the effectiveness and cost-effectiveness of an integrated, personalized and stepped care lifestyle approach for people with PD.

**Methods:**

We will perform a 12-month single-blind randomized controlled trial. We aim to include 256 people with PD, randomized in a 1:1 ratio into a control and intervention group. Both groups receive a clinical assessment with a lifestyle coach and can partake in usual care. The intervention group receives an additional lifestyle intervention, consisting of guidance and interventions on different lifestyle domains: stress, exercise, nutrition, sleep and self-management (the SENSS approach). This intervention is offered remotely according to a stepped care model to personalize the intervention to the participants’ needs and abilities. The primary endpoint is the between-group difference in quality of life at 12 months (Parkinson’s Disease Questionnaire-39). Secondary endpoints include between-group differences in PD symptoms, health-related outcomes, self-management and personal goals. Cost-effectiveness and the experiences of participants and healthcare professionals will also be explored.

**Discussion:**

This study evaluates the effectiveness of an integrated personalized lifestyle intervention for people with PD on both clinical and socio-economic outcomes. We expect this intervention to improve quality of life and self-management of people with PD, without increasing healthcare costs. We also expect to offer valuable insights into how such an intervention can be integrated into current daily care for people with PD.

**Clinical trial registration:**

ClinicalTrials.gov, identifier NCT06669455.

## Introduction

1

### Background and rationale

1.1

Parkinson’s disease (PD) is one of the most common neurological disorders, with a prevalence of almost 12 million people worldwide (1). People with PD often experience both motor and non-motor symptoms, which greatly impact their quality of life (QoL) (2, 3). Currently, there is no cure for PD. Medical management, including medication or deep brain surgery, can provide symptomatic relief, but this is often insufficient to alleviate all symptoms (4). In addition, the responsiveness to dopaminergic medication differs between individuals and across symptoms, and the effects wear off over time (5). Therefore, lifestyle interventions are increasingly recognized as a valuable additional way to support people with PD (6).

Lifestyle includes six pillars: physical activity, nutrition, stress management, restorative sleep, social connection and risky substance avoidance (7). Among these, physical activity, optimal nutrition, stress management and sleep have received most attention in research and clinical practice. Exercise attenuates motor- and non-motor symptoms and increases QoL, and may perhaps affect disease progression (8–10). There is also growing excitement about the potential role of other lifestyle interventions. Dietary interventions can have multiple benefits. For example, optimal fluid and fiber intake may reduce constipation and thereby increase medication effectiveness (11). In addition, a well-balanced intake of proteins and dopaminergic medication is important: proteins can compete with dopaminergic medication by causing malabsorption in the gut and brain, thus limiting its efficacy (12). At the same time, proteins are essential for body composition and muscle preservation. A lack of protein consumption may cause malnutrition and underweight (13). Underweight is a well-known indicator of negative health outcomes and also increases the risk of mortality (14). Another important factor related to nutrition is the gut microbiome, which plays a role in the pathophysiology of PD by impacting on, e.g., mitochondrial functioning, inflammation and immune responses (13). Although the evidence from robust clinical trials remains limited, there is enough reason to motivate people with PD to adhere to a healthy diet with adequate intake of macronutrients as suggested by organizations such as the World Health Organization (WHO) (15). The other lifestyle domains have been studied less well. However, emerging evidence shows that stress-reducing interventions, such as mind–body exercises and mindfulness-based interventions (MBIs), can reduce, e.g., anxiety and depression for people with PD, thus improving QoL (16–19). Moreover, positive effects of sleep hygiene education in people with PD with sleep disturbances have been found (20, 21).

So far, no studies have investigated the effects of interventions including multiple lifestyle domains in people with PD. While all domains are expected to have positive effects in isolation, they may even have a larger, additive and perhaps even synergistic effect when delivered in combination (6). Moreover, no studies have evaluated the cost-effectiveness of offering lifestyle interventions in PD.

In the absence of robust studies on effectiveness and cost-effectiveness, lifestyle interventions are currently not routinely offered as part of standard medical care. Consequently, people with PD receive hardly any guidance related to lifestyle changes. Based on interviews and our own clinical experience, we identified that many healthcare professionals in the Netherlands are not trained to provide lifestyle information or to offer personalized coaching (22, 23). Lifestyle coaches have the potential to play a role as a central coordinator of lifestyle interventions with expertise on all lifestyle domains and capable of coaching toward behavioral change (24, 25). The potential of lifestyle coaches has been shown in other chronic conditions (24, 25). Of note, changing lifestyle behavior is an enormous challenge for people with PD, especially when one needs to sustainably change multiple lifestyle aspects (26, 27). Therefore, a personalized approach, taking into account potential barriers related to lifestyle behavior is needed.

Motivated by these considerations, we here propose to combine different lifestyle domains into one approach as part of a personalized and stepped care lifestyle intervention. This approach, called the SENSS approach (stress, exercise, nutrition, sleep and self-management), is based on a combination of previous pilot initiatives (22, 28–32). A stepped care approach, with limited guidance when possible but with access to more intensive treatment when necessary, will deliver personalized care without further straining an already overburdened healthcare system. We expect that such a stepped care approach minimizes the extra costs for providing lifestyle guidance, yet lead to benefits of a healthy lifestyle. We expect this approach to be associated with a reduction of (long-term) healthcare costs, an increased productivity of people with PD and their caregivers and an improved QoL.

### Objectives

1.2

Our primary objective is to evaluate the effect of the SENSS approach on QoL in people with PD. Our secondary objective is to evaluate the effects of SENSS on PD motor- and non-motor symptoms, self-management, overall health and attaining personal lifestyle goals. A third objective is to analyze the costs and (socio-)economic impact of SENSS compared to current usual care. Our fourth objective is to evaluate the experiences of participants, lifestyle coaches and healthcare professionals with the SENSS approach.

Figure 1 provides an overview of the key elements of the SENSS intervention and the expected outcomes.

**Figure 1 fig1:**
[figure not shown]
Logic model SENSS.

## Methods

2

### Trial design

2.1

The SENSS study is a 12-month single-blind, randomized controlled trial (RCT). The intervention group receives a combined lifestyle intervention (SENSS approach) after a personalized intake and with continuous monitoring by a lifestyle coach. The control group only receives the personalized intake with a lifestyle coach, but continues with usual care. A total of 256 individuals with PD will be included, equally randomized into the control and intervention group. Participants complete three remote assessments: at baseline, 6 months, and 12 months follow-up. An overview of the study design is provided in Figure 2.

**Figure 2 fig2:**
[figure not shown]
Overview of study design.

### Study setting

2.2

The study will be performed by the Radboud University Medical Center (Radboudumc), Nijmegen, the Netherlands. The assessments and interventions of the study will be provided remotely. The study will be conducted in the Netherlands. People with PD will be recruited through a number of open recruitment strategies (see the section on recruitment strategies).

### Eligibility criteria

2.3

Inclusion criteria are: a confirmed diagnosis of PD by a neurologist according to established diagnostic criteria, and being able to read and understand the Dutch language. The exclusion criteria are: cognitive impairments that do not allow to complete the questionnaire, as judged by the researcher during the screening call; not in possession of or no access to an electronic device that allows for (video) calls with a lifestyle coach and to complete the questionnaires; planned surgery or an expected major change in treatment plan; participation in other intervention trials during the participation of the SENSS study.

### Who will take informed consent?

2.4

If a potential participant shows interest in the study, an assessor from the research team sends an information letter and informed consent through mail. After 2 weeks the assessor will contact the participant to answer questions, to check for eligibility and to discuss consent. When the participant is eligible and willing to participate, written informed consent will be obtained by signing the consent form and sending it to the research team by post. If an informal caregiver is available who is willing to fill out questionnaires, (s)he will receive an information letter and sign an informed consent as well. Participation of the informal caregiver is not mandatory for the participant to be included and does not influence the intervention in any way.

### Intervention

2.5

The intervention is a personalized and stepped care lifestyle intervention (SENSS) that combines five different and complementary lifestyle domains (stress, exercise, nutrition, sleep and self-management). In this intervention, self-management complements four important lifestyle domains, as it plays an overarching role in lifestyle behavior.

In the SENSS approach, participants receive guidance by a trained lifestyle coach. The title of lifestyle coach is not legally protected in the Netherlands. To ensure intervention quality, lifestyle coaches delivering the intervention are required to be affiliated with the Dutch professional association for lifestyle coaches (Beroepsvereniging Leefstijlcoaches Nederland; BLCN). BLCN affiliation requires compliance to strict admission standards and ongoing professional development. This includes holding at least a bachelor’s degree at a university of applied sciences level and having completed a BLCN-accredited postgraduate lifestyle coaching program, or having successfully completed an individual accreditation pathway (33). For this trial, two certified and dedicated lifestyle coaches will provide the intervention. Participants are divided pragmatically between the two lifestyle coaches, based on coach availability at the time of enrolment.

The SENSS approach starts with goal setting using a lifestyle decision aid, previously developed by our group in accordance with the International Patient Decision Aid Standards (22, 34). The Parkinson lifestyle decision aid (35) is a web-based tool. The tool includes information and questions that support people with PD to identify their needs in relation to lifestyle, set goals, make a plan, and determine the type of support they may need. The questions range from mapping the current situation in relation to their lifestyle, to clarifying their values, preferences and goals for all five lifestyle domains and identifying the needs for support to reach sustainable changes in lifestyle. The decision aid concludes with a summary of the answers given. This summary serves as a starting point for the consultation with the lifestyle coach, during which shared decision making is used to determine which lifestyle domain(s) to prioritize and what level of support is appropriate. For the participants in the intervention group, this level of support is further specified in a stepped care model (Figure 3).

**Figure 3 fig3:**
[figure not shown]
The stepped care model.

The stepped care model is used to provide just the right amount of guidance. By following the steps in the model, people with PD are encouraged to work on their lifestyle goals independently, supported by technological tools when possible (self-management). Professional support is provided when needed, based on participant reported needs and the lifestyle coach’s professional judgment. The approach is highly personalized, meaning participants do not have to follow a fixed sequence of steps. They can move between steps in either direction throughout the intervention. Importantly, a lifestyle coach will continuously monitor adherence and progress, and discusses with the participant whether changes are needed in either the lifestyle domain they are working on or in the level of support. The frequency of monitoring is decided through shared decision making by the lifestyle coach and participant, within a range of once every month to once every 3 months. In the following paragraphs the different steps will be described in more detail.

#### Step 1: working on lifestyle independently

2.5.1

Participants in step 1 are willing and able to work on their personal lifestyle goals independently, or with support from the people in their immediate environment. The lifestyle coach monitors the progress on the agreed intervals, as described in the previous paragraph.

#### Step 2: digital tools

2.5.2

Step 2 consists of support by digital tools. Tools have been selected for each lifestyle domain, based on previous work, mostly by members of our consortium. The lifestyle coach is responsible for monitoring the progress and actual usage of the tools in the domains stress, exercise, nutrition and self-management. For the online sleep training, a dedicated sleep therapist (a psychologist trained in behavioral sleep medicine) is involved. This approach is taken because sleep is only minimally addressed in current curricula for lifestyle coaches, and when it is included, specialized knowledge on PD-related sleep disorders is often lacking.

The following tools are available for this study: MindDistrict (mindfulness based stress reduction) (36, 37), STEPWISE (exercise) (38), Nutritional app by the Dutch “Voedingscentrum” (nutrition) (39), i-Sleep (sleep) (32), Parkinson in Balance (self-management) (30), and an online Parkinson Yoga library (multiple domains, including exercise and stress). More detailed information about the individual tools can be found in Supplementary material 1.

#### Step 3: remote coaching by lifestyle coach

2.5.3

When the participant needs more guidance than the online tools can provide, the next step includes remote personal coaching by the lifestyle coach (coaching mode). This differs from the continuous guidance provided throughout the stepped care model (guidance mode) in the frequency and content of the sessions. In the guidance mode, the lifestyle coach monitors the progress throughout and evaluates whether other approaches are needed. The progress is evaluated by discussing interim goals with participants. These evaluations are documented by the coach for clinical purposes and not included as research data. In the coaching mode, active coaching is provided to support the participant in changing behavior within a specific lifestyle domain. The number of sessions will be decided upon in mutual agreement with the participant, but this will be more frequent than in the guidance mode. Although the focus shifts to one-on-one guidance, the digital tools from step 2 can still be used to support the lifestyle change. Lifestyle coaching is, at this point, not part of the formal care pathways for people with PD. Lifestyle coaches in this study are trained to reach a sufficient level of PD-specific expertise, analogous to the way we train other allied health professionals as part of the Dutch national ParkinsonNet approach (40, 41). Examples of PD specific issues that may interfere with adherence to lifestyle advice include frontal executive problems, difficulties with dual tasking, fatigue and complex changes in the effectiveness of symptomatic pharmacotherapy. An essential part of the training of lifestyle coaches is to clarify which other professionals within ParkinsonNet can offer further detailed guidance, if the lifestyle coach feels insufficiently equipped to address a particular issue himself or herself (see step 4). Furthermore, they are trained to recognize PD related red flags (such as unintended weight loss or balance problems) requiring referral to healthcare professionals (step 4).

#### Step 4: treatment by specialized healthcare professional

2.5.4

Some participants may experience specific barriers or problems, such as PD related red flags, that hinder making lifestyle changes and require more expertise. These participants can be referred to specialized healthcare professionals (e.g., a physiotherapist, dietician, psychologist or social worker). In the Netherlands, specialized allied healthcare is organized as part of the Dutch ParkinsonNet approach, with national coverage. Cost-effectiveness of ParkinsonNet has been shown in multiple studies (42, 43). Because ParkinsonNet currently does not include somnological treatment, a sleep medicine center (Kempenhaeghe) is involved, where specialized care for sleep disorders can be provided, and in which extensive experience is available on sleep and PD. In this study, all referrals to specialized care will be made through standard healthcare procedures in the Netherlands (i.e., the general practitioner overseeing the participant’s care).

#### Strategies to improve adherence to intervention

2.5.5

Several strategies to improve adherence are an inherent part of the SENSS approach, starting with the Parkinson lifestyle decision aid. The intervention is fully personalized to the participants’ needs and abilities, and can be adapted to changes along the way. Additionally, adherence to the intervention is monitored by the lifestyle coach during the structural contact moments.

#### Relevant concomitant care permitted or prohibited during the trial

2.5.6

Both the control and intervention group will receive usual care. Participants in the control group are allowed to use any intervention or digital tool that is (publicly) available that may support them in a healthy lifestyle. However, most digital tools that are used in the intervention group are not publicly available, and therefore not accessible by the control group (MindDistrict, STEPWISE, i-Sleep, Parkinson in Balance, and the online Parkinson Yoga library are not publicly available). Apart from those digital tools, participants are not restricted in any type of care they use.

### Outcomes

2.6

#### Primary outcome

2.6.1

The primary outcome is the between-group difference in QoL from baseline to 12 months (end of intervention) measured with the Parkinson’s Disease Questionnaire-39 (PDQ-39) (44). The PDQ-39 is the most widely used QoL scale in PD, frequently used as the outcome measure, e.g., in trials on deep brain stimulation, multidisciplinary care and allied health interventions (45, 46). This questionnaire assesses the impact of PD on a person’s QoL. It consists of 39 questions across eight dimensions of daily living including relationships, social situations and communication. Item scores are filled out on a 5-point scale from “never” to “always.” Both the total score of the PDQ-39 and the scores for each of the eight dimensions are considered primary outcomes.

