### Sample size

2.8

Based on a recent systematic review on self-management interventions in people with PD (71) we identified two RCT’s (72, 73) that have studied a self-management intervention including lifestyle advice for people with PD using the PDQ-39 as an outcome. While the present intervention is much more comprehensive and personalized and includes more coaching and guidance when needed, we decided to conservatively use the results of those studies for our sample size calculation. Both studies found a mean between group difference of 4.15 on the PDQ-39, with a mean standard deviation of 10.55. With a significance level of 0.05 and 80%, we need 102 participants per group. Assuming 20% dropouts, we will include 128 participants per group (256 in total).

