#### Sequence generation

2.10.1

After completing the baseline questionnaires, eligible participants will be randomly allocated to the intervention group or the control group in a 1:1 ratio. Randomization will be performed in the data management system CastorEDC (75) using random block sizes (block sizes: 4, 6, 8). We will stratify the randomization based on disease duration, categorizing participants into three groups: <5 years, 5–10 years, and >10 years since disease onset. The randomization will be performed by a researcher who is not involved in the measurements and data analysis. The study is single-blinded. The researcher performing the analyses is not aware of treatment allocation.

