##### Primary outcomes

2.15.1.1

The primary endpoint is the difference between groups in QoL (PDQ-39) over 12 months’ time. A linear mixed model (LMM) with repeated measurements will be used to evaluate the changes over time between the intervention and control group. The primary outcome and dependent variable is the total score of the PDQ-39, with additional models fitted for each of the eight domain scores. We include fixed effects for group, time (T0, T1 and T2) and the interaction between group and time. Sex, age, and disease duration at baseline will serve as covariates. Random effects will be included for participants to account for within-subject correlation and for lifestyle coaches to account for clustering by coach.

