#### Methods for additional analyses

2.15.2

Exploratory mediation analyses will be performed on the primary outcome (PDQ-39 total score) to assess the potential mediating role of psychosocial constructs, including general self-efficacy (GSES), coping style (WCQ), and self-management (PAM). Exploratory subgroup analyses will be conducted to investigate effects based on the specific lifestyle domain participants focused on during the intervention. Specifically, we will explore (1) whether there are differences in QoL between participants who targeted different lifestyle domains, (2) multiple lifestyle domains versus a single domain, and (3) whether participants show improvements in outcomes directly related to the domain they worked on. For example, whether those who focused on the sleep domain demonstrate an improvement in insomnia and sleep quality. We hypothesize that participants may show greater improvements in outcomes directly related to the lifestyle domain they actively targeted. Furthermore, we will perform exploratory subgroup analyses based on disease duration. Participants will be categorized into three groups: <5 years, 5–10 years, and >10 years since disease onset.

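### The protocol makes nine PDQ-39 scores primary in section 2.6.1 but only the total score in sections 2.15.1.1 and 2.15.2, and the sample size provides for one test

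*Protocol article*

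**What the plan says.** The protocol article describes the primary outcome in several places.

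- **Section 2.6.1 (Primary outcome)** opens in the singular, with the PDQ-39 as the measure, and closes with "Both the total score of the PDQ-39 and the scores for each of the eight dimensions are considered primary outcomes". That is one total plus eight dimensions, nine primary outcomes.
- **Section 2.15.1.1 (Primary outcomes, statistical methods)** says "The primary outcome and dependent variable is the total score of the PDQ-39, with additional models fitted for each of the eight domain scores". That is one primary outcome.
- **Section 2.15.2 (additional analyses)** agrees with 2.15.1.1: "Exploratory mediation analyses will be performed on the primary outcome (PDQ-39 total score".
- **The abstract** also names one endpoint: "The primary endpoint is the between-group difference in quality of life at 12 months".
- **Section 2.8 (Sample size)** plans one comparison: "Both studies found a mean between group difference of 4.15 on the PDQ-39, with a mean standard deviation of 10.55", then "With a significance level of 0.05 and 80%, we need 102 participants per group", then "Assuming 20% dropouts, we will include 128 participants per group (256 in total". It refers to the PDQ-39 without naming the total score, but it uses one difference, one SD and one significance level.

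The article gives no order of testing, no adjustment and no rule for calling the trial positive across nine scores. The 0.05 appears only in the sample size section.

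**The concern.** The primary outcome decides what counts as a positive trial, and here two sections define it differently. Suppose the total score shows no clear difference while one dimension, say communication, reaches p < 0.05. Under section 2.15.1.1 the primary result is negative. Under section 2.6.1 the same data could be presented as a positive result on a primary outcome. Two honest readers could report opposite conclusions.

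Two quantities are at stake. One is the chance of a false positive primary claim if the nine-outcome reading were used with no adjustment. The other is power if that reading were kept and adjusted, since the trial was sized for one test.

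**Working it through.** **Inputs from the protocol.** Difference 4.15, SD 10.55, significance level 0.05, power 80%, 20% dropout (section 2.8); 1:1 allocation (section 2.10.1); nine scores (section 2.6.1). Sidedness is not stated.

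**Step 1: reproduce the planned sample size as one test.**

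n per group = 2 × (z₀.₉₇₅ + z₀.₈₀)² × (SD/difference)²
= 2 × (1.960 + 0.842)² × (10.55/4.15)²
= 2 × 7.85 × 6.46 ≈ 101.5, so 102.

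With 20% dropout: 102/0.8 = 127.5, so 128 per group and 256 in total. The plan's figures are reproduced. Power at 102 per group is 80.2%. A one-sided test would need only 80 per group, so the plan's 102 is a two-sided test at the full 0.05. (The t-based version gives 102.4.) No part of the 0.05 is left for other primary tests.

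**Step 2: family-wise error if any one of nine scores at 0.05 counted, with no adjustment.**

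For nine fully independent tests: 1 − 0.95⁹ = 0.370.

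The total is built from the dimensions, so full independence is not realistic. I simulated eight equally correlated null z-statistics, took the total as their standardised mean, and counted how often at least one of the nine exceeded 1.96 in absolute value (500,000 draws per row). The document gives no correlations, so these are assumptions shown as a range.

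| Assumed correlation between dimensions | Chance of at least one false positive among nine |
|---|---|
| 0 | 35% |
| 0.3 | 30% |
| 0.5 | 25% |
| 0.7 | 19% |
| 0.9 | 12% |

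Other success rules give other answers. If the total alone decides, the error is 5%. If all nine had to be significant, it would be at most 5%, with lower power.

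**Step 3: power if nine primaries were kept and adjusted.**

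Equal-split Bonferroni: 0.05/9 = 0.00556, two-sided critical value about 2.773. The document gives no effect or SD for any dimension, so 4.15 and 10.55 are assumed for each score.

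- Expected z at 102 per group: (4.15/10.55) × √(102/2) = 0.3934 × 7.141 = 2.809.
- Power per score: Φ(2.809 − 2.773) = Φ(0.036) ≈ 51.4% (50.4% by the t-test).
- Needed for 80%: 2 × (2.773 + 0.842)² × 6.46 ≈ 168.9, so 169 per group (171 by the t-test). After dropout, 169/0.8 = 211.25, so 212 per group and 424 in total, against 256 planned.

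Under a fixed sequence that tests the total first at the full 0.05 and the dimensions only afterwards, power for the total stays at the 80.2% of step 1.

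**The case against.** The best defence is that only one sentence is out of line. The section that governs the analysis, the mediation analyses, the abstract and the sample size all point to a single primary outcome, and section 2.6.1 itself starts in the singular. On that reading the error rate is 5% and the planned power stands. The article is also condensed, and a testing procedure may sit in the full protocol or the statistical analysis plan, neither of which is shown.

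Much of this stands. A reader might infer that the trial will test nine scores at an unadjusted 0.05, that any one of them would count as success, and that its error rate is therefore not 5%. The document does not support that. No section sets a threshold for the dimension scores or an any-of-nine rule, and silence on adjustment in a condensed article is not evidence that there is none. Nor does adjusting nine primaries always cost power: the loss in step 3 belongs to equal-split Bonferroni. The roughly 50% there is also power for one given score, while the error rates in step 2 concern any of nine, so the two should not be read as one scenario.

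The contradiction remains. An analysis plan can choose between one and nine primary outcomes, but it cannot make both published statements true. If nine were intended with an equal split, section 2.8 would also need to change.

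**Conclusion.** The protocol contradicts itself on what its primary outcome is, and this should be settled before any unblinded analysis. The contradiction rests on the text alone and needs no assumption.

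The consequences are conditional. Under an unadjusted any-of-nine rule, the family-wise error would be roughly 12% to 35% for correlations of 0.9 to 0, with the total taken as the mean of eight equally correlated dimensions; 37% applies only to nine fully independent tests. Under an equal-split Bonferroni correction, with the planned effect assumed for every score, power per score would be about 50%. If the total alone is primary, neither consequence arises. It would go too far to say that the trial's error rate is inflated as planned, because the article does not state the rule that would inflate it.

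**What to change.** Replace the last sentence of section 2.6.1 with: *The single primary outcome is the PDQ-39 total score; the eight dimension scores are secondary.* This agrees with sections 2.8, 2.15.1.1 and 2.15.2.

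Report the eight dimensions with confidence intervals. If claims on them are wanted, test them after the total by a procedure that controls multiplicity, such as Holm among the eight once the total is significant.

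The registry entry was not available for this review. It should be checked for consistency, and no discrepancy is alleged.

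The cost is wording only. The sample size stays at 256 and the model does not change. The sponsor gives up the option of a primary claim on a single dimension. Timing matters: the trial status section reports 219 participants randomised and none finished at 20 November 2025, with the first inclusion on 25 November 2024, so 12-month data were about to arrive. A change dated before unblinded results are seen is credible; a later one could look like a choice made on the results.
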